### Randomization method

All patients included are routinely followed in the spasticity-units of the three participating centers. All will already be treated with BTX-A and will have undergone regular spasticity ratings using the MAS. Patients with spasticity of both the RF and TS will therefore be identified before the study is presented to them during visit 1. In addition, all patients will already have undergone routine 3D gait analysis as part of their management, thus the decrease in peak knee flexion and peak ankle plantarflexion in swing phase will already be documented, with the cause reported as RF and TS spasticity. Randomization will be carried out using randoWeb software (http://randoweb.aphp.fr) at the beginning of visit 2, then either BTX-A or the placebo will be injected according to group allocation. To avoid problems relating to expiration of the BTX-A, the BTX-A and placebo packs will be randomized, not the patients. A randomization list will be uploaded on a dedicated server (CleanWeb) and each patient will be attributed an injection pack number. The randomization will be block-balanced. Patients will thus be injected with either BTX-A or the placebo at visit 2.

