### Secondary aim: Outcomes

The secondary outcomes are peak muscle force generated during gait assessed by the MSM, peak force measured during the isometric evaluation, inter-segmental coordination during gait assessed by 3D analysis, and functional tests.

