## Statistical analysis

### Sample size calculation

Sample size was estimated using G*power software [59]. The input data were taken from Lampire et al. [15] who assessed the effect of BTX-A injection on length and lengthening velocity of rectus femoris during gait in chronic stroke patients). Using a two-tailed test at a threshold of 5% and a power of 80%, a sample of seventeen subjects per group was found to be necessary [60]. We therefore plan to recruit forty patients to take into account potential patients lost to follow-up. The study is currently underway. On the first of April 2018, twenty-eight participants had been included.

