#### Analysis of primary outcome

Change in peak length of the RF and TS muscles during gait at 1 month (difference in length between V3 and V1 will be compared between groups using a Student t-test. To prevent the risk of false positives induced by multiple testing, a Bonferroni Holm correction will be applied to the *p*-values for peak length, peak force and peak strength [61]. The level of significance will be set at 0.05/3.

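### The primary analysis names a Bonferroni-Holm correction for three p-values and also fixes the level at 0.05/3; taken literally this corrects twice, and on any other reading the rule contradicts or misdescribes Holm.

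*Protocol article*

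**What the plan says.** Under *Analysis of primary outcome*, the change in peak muscle length from V1 to V3 is compared between groups with a Student t-test. To limit false positives, "a Bonferroni Holm correction will be applied to the" p-values of three parameters: peak length, peak force and peak strength. The next sentence reads: "The level of significance will be set at 0.05/3". Nothing there says that 0.05/3 is meant only as the first of Holm's steps.

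The status of the three parameters varies. *Primary aim: Outcome* names only the change in maximal muscle length. *Secondary aim: Outcomes* begins: "The secondary outcomes are peak muscle force generated during gait assessed by the MSM, peak force measured during the isometric evaluation". Table 2, however, lists peak strength under the first aim.

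*Sample size calculation* uses a two-sided 5% level and 80% power, with no allowance for multiplicity, and reports that "a sample of seventeen subjects per group was found to be necessary". It continues: "We therefore plan to recruit forty patients to take into account potential patients lost to follow-up". It refers to a pilot study for its inputs but prints no effect size or standard deviation.

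**The concern.** Holm can be written in two equivalent ways: adjust the p-values and compare them with 0.05, or leave them raw and compare them in order with 0.05/3, 0.05/2 and 0.05. The plan takes the adjustment from the first form and a threshold from the second, and then holds that threshold fixed. An analyst who follows both sentences applies the factor of three twice.

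The primary conclusion may depend on the choice. Suppose peak length has the smallest of the three p-values, with a raw value of 0.010. Its Holm-adjusted value is 3 × 0.010 = 0.030, which is significant against 0.05 and not significant against 0.0167. Two analysts could report opposite results from the same data while each claims to follow the protocol. Settling the matter after unblinding would be a data-dependent choice.

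**Working it through.** **Inputs from the protocol article.** Family of three tests and the threshold 0.05/3 (*Analysis of primary outcome*); two-sided 5%, 80% power, 17 per group and 40 recruited (*Sample size calculation*). Equal groups are assumed, so 40 recruited means 20 per group; the article says "The randomization will be block-balanced" and gives one size for both groups.

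**1. Thresholds under each reading.**

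| Reading | Smallest p | Middle p | Largest p | Family-wise level |
|---|---|---|---|---|
| Holm-adjusted p against 0.05/3 (literal) | 0.0167/3 = 0.0056 | 0.0167/2 = 0.0083 | 0.0167 | about 1.7% |
| Raw p against a fixed 0.05/3 (plain Bonferroni) | 0.0167 | 0.0167 | 0.0167 | at most 5% |
| Holm | 0.05/3 = 0.0167 | 0.05/2 = 0.025 | 0.05 | at most 5% |

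For the literal reading with three independent true nulls: 1 − (1 − 0.0056)³ ≈ 1.7%.

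**2. The plan's own sample size.** Without an effect size, 17 per group cannot be reproduced independently. It can be inverted. For a two-sample t-test, power is the probability that a noncentral t variable, with 2n − 2 degrees of freedom and noncentrality d√(n/2), exceeds the two-sided critical value. Setting n = 17, level 0.05 and power 0.80 gives d = 0.991. Any d from 0.991 to 1.024 rounds up to 17. The noncentrality at d = 0.991 is 0.991 × √8.5 = 2.89 for 17 per group and 0.991 × √10 = 3.13 for 20 per group.

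**3. Probability that peak length passes a given raw threshold, d = 0.991.**

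| Raw threshold | 17 per group | 20 per group |
|---|---|---|
| 0.05 (no correction) | 80% | 86% |
| 0.05/3 = 0.0167 (Holm, first step) | 64% | 73% |
| 0.05/9 = 0.0056 (literal rule, first step) | 48% | 58% |

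These are marginal probabilities of passing a fixed threshold. They are not conditional on peak length having the smallest p-value.

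**4. Sensitivity to d.** At d = 1.024 the bottom row becomes 51% and 62%. With the normal approximation and its own back-solved d of 0.961, it becomes 51% and 60%.

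**5. Full step-down procedure**, simulated with 200,000 runs at correlations of 0 and 0.5. The figures are power for peak length.

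| Other two endpoints | Rule | 17 per group | 20 per group |
|---|---|---|---|
| No effect | Holm at 0.05 | 64% | 73–74% |
| No effect | Literal rule | 48% | 58% |
| Same effect | Holm at 0.05 | 73–74% | 81–83% |
| Same effect | Literal rule | 55% | 66% |

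**6. Splitting the loss at 20 per group.** From 86% to 73% is 13 points, caused by a single correction that the sample size ignored. From 73% to 58% is 15 points, caused by the second correction. At this d, 80% power at a threshold of 0.05/3 needs about 23 per group; at 0.05/9 it needs about 29.

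**The case against.** The best defence is that 0.05/3 is exactly Holm's first threshold for three tests, so the sentence may be shorthand for where the procedure starts. If so, nothing is corrected twice and the 58% does not arise. That is plausible, and double correction cannot be called the established intention. But the text gives one level without qualification, and Holm has no single level, so the sentence would still misdescribe the rule.

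It is also fair to say that no reading lets the family-wise error exceed 5%. This is not a false-positive problem.

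Four stronger inferences are tempting, and the documents do not support them:

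- **That the trial's power is 58%.** This figure needs a back-solved effect the article does not state, all 40 patients analysed, and the strictest step.
- **That the whole fall from 86% to 58% comes from correcting twice.** Nearly half comes from the single correction.
- **That any raw p-value for peak length between 0.0056 and 0.0167 fails under the literal rule.** It fails when peak length has the smallest p-value. With raw values 0.002, 0.005 and 0.012, the last being peak length, the Holm-adjusted values are 0.006, 0.010 and 0.012. All are below 0.0167, so peak length passes.
- **That peak length plainly pays for two secondary outcomes.** *Secondary aim: Outcomes* supports this, but Table 2 puts peak strength under the first aim.

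**Conclusion.** The point holds as a defect in the stated decision rule. The two sentences are a double correction if taken literally, a contradiction if the second means plain Bonferroni, and a misdescription if it means only Holm's first step.

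On the literal reading, power for peak length lies between about 48% and 66% across 17 to 20 per group and across no effect or an equal effect on the other two endpoints, at the assumed d of about 0.99. Every scenario computed under that reading is below the 80% target. Compared with correct Holm, the second correction costs roughly 15 to 19 points. The certain cost is the ambiguity: when peak length has the smallest p-value and that value lies between 0.0056 and 0.0167, the primary conclusion depends on which reading the analyst picks.

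**What to change.** Before unblinding, delete the sentence that sets the level at 0.05/3 and replace it with: *Holm-adjusted p-values for the three tests are compared with 0.05 (equivalently, the ordered raw p-values are compared with 0.05/3, 0.05/2 and 0.05).* This keeps the family-wise error over the three tests at 5%.

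The sponsor may prefer to test peak length first at 0.05, since *Primary aim: Outcome* names it alone. Force and strength must then follow in a fixed order, or with Holm applied between them. Testing both at an unadjusted 0.05 once peak length succeeds could give a family-wise error of 1 − 0.95² = 9.75% if both are null and independent. This option also requires *Secondary aim: Outcomes* and Table 2 to be reconciled on the status of peak strength.

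The cost is one sentence and the amendment that *Management of changes to the planned analysis* already foresees. No further patients are needed to make the rule coherent. The power at the chosen rule should be stated beside it, because the sample size calculation makes no allowance even for a single correction.

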#### Analysis of secondary outcomes

The statistical test used for the primary outcome will also be used to evaluate the effect of BTX-A at 3 months (V4). To compare changes in the secondary criteria across visits between the two groups (change in peak length of injected muscles, joint angles, modified Ashworth score, functional scores and quality of life), repeated measures models will be used. Depending on the distribution of continuous or binary variables, mixed models or generalized estimation equations (GEE) will be used respectively. The models will include the treatment variable (BTX-A or placebo), time and interaction between time and treatment as explanatory factors. If a significant interaction is found, comparisons between both groups (BTX-A and placebo) will be carried out for each time-point using a Student t-test. In order to take in to account any effects of multiple testing, these outcomes will be considered as explanatory factors rather than determinants of the effectiveness of BTX-A.

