### Study design

The study will be prospective, 3-centre, randomised, placebo-controlled and triple blinded. The total duration of the study will be 36 months. The duration of participation of each patient will be 3 months, with four visits. The patients and the injecting doctors and assistants, as well as the evaluators will be blinded to the patients’ group allocations. Randomization will be carried out by computer software. During visits V1, V3 and V4 the measurements will be carried out throughout the day with breaks allowed between each (Table 1).

**Table 1 Tab1:** Tests and evaluations during each visit

Tests and evaluations	V1	V2	V3	V4
Inclusion/ exclusion criteria	X			
Informed consent	X			
Randomisation	X			
Injection BTX-A or placebo		X		
Evaluation of passive range of motion (MG)	X		X	X
Evaluation of spasticity (MAS)	X		X	X
Evaluation of strength (MRS)	X		X	X
SF 36	X		X	X
FIM	X		X	X
ABILOCO scale	X		X	X
Berg balance scale	X		X	X
Abc scale	X		X	X
Timed up and go	X		X	X
3D analysis	X		X	X
Isokinetic evaluation	X		X	X

*V1* visit 1, *V2* visit 2, *V3* visit 3, *V4* visit 4, *MA* manual goniometer, *MAS* modified Ashworth, *MRC* Medical Research Council, *SF36* The Short Form (36) Health Survey, *FIM* Functional independence measure, *3D analysis* gait motion analysis. All outcome measures will be evaluated during the first visit (baseline-V1) and 1 month (V3) and 3 (V4) months after injection. All evaluations will be performed in the same order at each session in order to limit bias related to fatigue

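### For the repeated-measures secondary outcomes, visit comparisons wait on a significant interaction, which can withhold them when an effect is maintained; peak length at 3 months has two analyses

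*Protocol article*

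**What the plan says.** Outcomes are measured at three visits: "All outcome measures will be evaluated during the first visit (baseline-V1) and 1 month (V3) and 3 (V4) months after injection". The section Analysis of secondary outcomes uses these in two ways.

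- Peak length at 3 months: "The statistical test used for the primary outcome will also be used to evaluate the effect of BTX-A at 3 months (V4"). The primary test is a t-test on the difference between V3 and V1 (Analysis of primary outcome), so peak length has an ungated comparison of change at both visits.
- Other secondary criteria: repeated measures models are fitted "To compare changes in the secondary criteria across visits between the two groups". The list in brackets covers joint angles, Ashworth score, functional scores and quality of life, and it includes change in peak length again. The model terms are treatment, time and their interaction, with no separate baseline covariate. Then: "If a significant interaction is found, comparisons between both groups (BTX-A and placebo) will be carried out for each time-point using a Student t-test".

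The same section says that these outcomes do not determine the effectiveness of the toxin. The section on changes to the planned analysis gives, as a second aim, finding out whether the effects are still present at V4 relative to V1.

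**The concern.** The secondary questions are how large the treatment difference is at 1 month and whether it lasts to 3 months. A time-by-treatment interaction answers a different question: whether the difference varies between the levels of time. What that means depends on the response, which the section leaves open.

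- If the response is change at V3 and V4, the interaction tests whether the V4 effect differs from the V3 effect. The better an effect is maintained, the less likely the visit comparisons are to be made.
- If the response is the value at V1, V3 and V4, a maintained effect is itself an interaction. The gate is then only an extra 2-df hurdle.

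The wording leans towards changes but does not settle it. A maintained effect is not a remote scenario: the Background puts the duration of action at around 3 months, and the Discussion expects effects at 1 month and perhaps at 3. At stake are the per-visit results for function, spasticity and quality of life, and a clear answer for peak length at V4.

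**Working it through.** **Inputs.** From the article (Sample size calculation): 17 per group for 80% power at two-sided 5%, and 40 patients planned. Assumed: 1:1 allocation (the text says only "The randomization will be block-balanced"), equal variances, equal correlation ρ between visits (0.5, 0.7, 0.85), no missing data. Let n be patients per arm, d the V3 effect in SDs of change, and f the fraction of that effect left at V4.

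**1. The plan's own figure.** No effect size is printed, so 17 per group can only be solved backwards. With the noncentral t (32 df, noncentrality d√(n/2)), 80% power at n = 17 needs d = 0.991, noncentrality 0.991 × √8.5 = 2.89; n = 16 would need 1.024. Allowing 15% loss, 34/0.85 = 40, so the recruitment figure is coherent. At n = 20 the ungated t-test on change has power 0.86.

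**2. Changes at V3 and V4 modelled.** The interaction is the group difference in V4 minus V3. That difference has the same SD as a change from V1, so its standardised effect is d(1 − f), whatever ρ.

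- f = 1: effect 0, so the gate opens at its 5% error rate. This holds for any d.
- f = 0.5: effect 0.496; the gate opens in 0.29 (n = 17) or 0.33 (n = 20).

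The treatment main effect uses the mean of the two changes. Its variance is 1.5(1 − ρ) against 2(1 − ρ) for one change, so its standardised effect is d(1 + f)/2 ÷ √0.75. At f = 1 that is 1.144, with power 0.90 (n = 17) or 0.94 (n = 20).

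**3. Values at V1, V3 and V4 modelled.** The 2-df interaction test has noncentrality (n/2) × d² × (4/3)(1 − f + f²), again free of ρ. At n = 17 this is 8.5 × 0.982 × 1.333 = 11.13 for f = 1 and 8.5 × 0.982 × 1 = 8.35 for f = 0.5. At n = 20 it is 13.09 and 9.82.

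Joint power (gate opens and the V3 t-test on change is significant) was simulated, 20,000 trials per row at ρ = 0.7:

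| n per arm | f | V3 test, no gate | Gate, changes | Gate + V3 test, changes | Gate, V1 as level | Gate + V3 test, V1 as level |
|---|---|---|---|---|---|---|
| 17 | 1 | 0.80 | 0.05 | 0.03 | 0.82 | 0.74 |
| 17 | 0.5 | 0.80 | 0.29 | 0.27 | 0.69 | 0.68 |
| 20 | 1 | 0.86 | 0.05 | 0.04 | 0.88 | 0.82 |
| 20 | 0.5 | 0.86 | 0.33 | 0.32 | 0.77 | 0.76 |

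With V1 as a level, the loss at V3 runs from about 4 points (0.86 to 0.82) to about 12 (0.80 to 0.68).

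**4. Which values the follow-up t-test uses.** The text does not say. On raw V3 values the standardised effect is d√(2(1 − ρ)); with baseline as covariate it is d√(2/(1 + ρ)). At n = 17:

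| ρ | Raw effect | Raw power | Adjusted effect | Adjusted power |
|---|---|---|---|---|
| 0.5 | 0.991 | 0.80 | 1.144 | 0.89 |
| 0.7 | 0.768 | 0.58 | 1.075 | 0.85 |
| 0.85 | 0.543 | 0.34 | 1.030 | 0.82 |

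The adjusted powers are simulated; the formula gives up to 0.01 more because it ignores chance baseline imbalance. A t-test on change stays at 0.80 for every ρ.

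**The case against.** Four points count against a stronger claim.

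- A reader might infer that every comparison at 1 and 3 months sits behind the gate. It does not. Peak length is tested ungated on change at V3 and, by the first sentence of the secondary section, at V4. This stands.
- A reader might take the 5% figure as the plan's behaviour. It holds only if changes are modelled with V3 and V4 as the levels of time. Measurement at V1, V3 and V4, and a maintenance aim phrased relative to V1, fit the other reading equally well, and there the gate costs much less. Even under the change reading, the treatment main effect would usually show a maintained effect. What remains is that no rule lets the main effect open the visit comparisons.
- A reader might infer that baseline is thrown away. That is so only if the follow-up t-tests use raw visit values. The one t-test the article defines uses change, and there the gain from adjustment is modest: 0.80 against 0.82 to 0.89 at 17 per arm.
- The outcomes are declared non-confirmatory. That lowers the stakes, but it also removes the multiplicity argument for having a gate.

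A Student t-test after a GEE would be wrong for a binary outcome, but none of the listed outcomes is evidently binary, so this is loose wording. Defining the response might be left to an analysis plan that is not shown. The gate itself is fixed in the article.

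**Conclusion.** The point holds for the secondary outcomes analysed by repeated measures models, not for the primary test. The gate brings no benefit under either reading. Its cost ranges from about 4 to 12 points of V3 power to near-complete loss of visit comparisons for a maintained effect, and the article does not say which reading applies. Separately, peak length at V4 has an ungated and a gated route with no order of precedence.

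The 5% figure for a fully maintained effect under the change reading does not depend on the effect size. All other figures rest on d = 0.99, back-solved from a sample size based on rectus femoris length; the article gives no effect size for the gated outcomes. The figures that vary with correlation are shown for 0.5 to 0.85, which is also an assumption.

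**What to change.** - Delete the interaction condition and the follow-up t-tests.
- For each outcome, fit one model to V3 and V4 with the baseline value, treatment, visit and treatment-by-visit: a mixed model, or a GEE for any binary outcome. Report the treatment difference at V3 and at V4 with a 95% confidence interval, whatever the interaction p-value. This also settles the response and the levels of time.
- Name one analysis for peak length at V4.

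The cost is a change of wording, with no new data or patients. The drawback is that more estimates are reported; they stay labelled non-confirmatory, as the article already has them.

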#### Analysis of safety criteria

The number and percentage of patients who experience adverse expected or unexpected effects, as well as serious adverse effects relating to the active treatment will be analysed. The nature of each effect will be specified. The duration and percentages of any adverse effects following BTX-A injection will be compared with any that occur following placebo injection using non-parametric tests.

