### Management of adverse events

Patients will be informed about possible adverse events at the time of inclusion. If any adverse events occur, the study coordinator must be immediately contacted. Two types of adverse events will be considered.

Non-serious adverse events or effects are defined as any harmful manifestation that occurs in the subject, whether or not this manifestation is linked to any experimental element of the research or products used. Non-serious events may include: pain or burning at the injection site, injected limb pain, ecchymosis, hypertonia, muscular weakness, arthralgia, asthenia, hyperesthesia, pain, depression, insomnia, discomfort, nausea etc.

Serious adverse events or effects are any adverse event or effect that results in death, endangers life, requires hospitalization or prolongation of hospitalization, causes significant or lasting disability, or results in an anomaly or a congenital malformation. Undesirable effects whose nature, severity or evolution does not correspond to the information contained in the references recognized by the authorities are considered as serious, as are any adverse effects related to the diffusion of the BTX-A away from the injection site. Serious adverse events therefore include excessive muscle weakness, dysphagia, inhalation pneumonia, anaphylactic reactions etc.

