#### Sample analysed

Because this is a study of effectiveness, the main analysis will be carried out following intention to treat principles. The safety analysis will be carried out on all participants who received at least one injection, whatever the substance injected. For the safety analysis, participants will not be analysed according to treatment allocation, but according to the treatment actually received.

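### The serious-event count is worded by relation to the active treatment, which is inconsistent with the protocol's own definition of a serious event, its two-arm safety comparison and its all-injected safety set

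*Protocol article*

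**What the plan says.** Three places in the protocol article bear on the safety analysis.

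- **Analysis of safety criteria.** The opening sentence covers "The number and percentage of patients who experience adverse expected or unexpected effects", and continues: "as well as serious adverse effects relating to the active treatment will be analysed". The section closes with a two-arm comparison of how long effects last and how often they occur: "any adverse effects following BTX-A injection will be compared with any that occur following placebo injection using non-parametric tests".
- **Sample analysed.** "The safety analysis will be carried out on all participants who received at least one injection, whatever the substance injected". For this analysis, "participants will not be analysed according to treatment allocation, but according to the treatment actually received".
- **Management of adverse events.** "Serious adverse events or effects are any adverse event or effect that results in death, endangers life, requires hospitalization or prolongation of hospitalization"; lasting disability and congenital anomaly complete the outcome criteria. The non-serious category applies "whether or not this manifestation is linked to any experimental element of the research or products used". The coordinator must be contacted at once about any adverse event.

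**The concern.** The opening sentence of the safety analysis puts a causality condition on serious effects. No other sentence in the article says that serious events judged unrelated will be tabulated by arm.

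This matters because of the design. In a randomised, blinded, placebo-controlled trial, the placebo arm shows how often serious events occur without BTX-A. An excess in the BTX-A arm can then be seen without deciding the cause of each case. If events are first selected by attribution, that advantage is lost for the events that matter most.

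A hypothetical case shows the risk. A patient falls and is hospitalised, and the event is judged unrelated to the injection. On the literal wording it does not enter the serious-event count. Yet the article itself lists muscular weakness among the possible non-serious events and excessive muscle weakness among the serious ones, so a link between injection and fall is plausible. An imbalance in such hospitalisations between arms is something randomisation could reveal and an attribution filter could hide.

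**Working it through.** No arithmetic applies. The article gives no adverse-event rate, and the point depends on no sample size, power or significance level. The check is to set the statements side by side.

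1. **What is collected.** Under Management of adverse events, the main criteria for a serious event (death, danger to life, hospitalisation, disability, congenital anomaly) are outcomes with no causality condition. Two further clauses do refer to the product: effects that do not match the recognised reference information, and effects from diffusion of the toxin. They add to the list and do not narrow the outcome criteria. The non-serious definition sets causality aside expressly.

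2. **What is counted as serious.** Under Analysis of safety criteria, the serious effects to be analysed are those related to the active treatment. This is a subset of item 1.

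3. **What is compared.** The last sentence of that section compares any effects after BTX-A with any after placebo. Its link to the injection is one of time, and it names no causality condition. A two-arm comparison needs one event definition that works the same way in both arms, and relation to the active treatment is a poor definition for patients who received saline.

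4. **Who is included.** Under Sample analysed, all injected patients are in the safety set, grouped by treatment received. Placebo recipients are there deliberately.

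Applied to a serious event, the wording gives this:

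| Serious event | Collected | Serious-event count, read literally | Closing two-arm comparison |
|---|---|---|---|
| BTX-A arm, judged related | Yes | In | In |
| BTX-A arm, judged unrelated | Yes | Out | Unclear |
| Placebo arm, judged related (possible if judged blind) | Yes | In, if the blinded judgement is what counts | In |
| Placebo arm, judged unrelated | Yes | Out | Unclear |

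The entries marked unclear arise because the closing sentence speaks of any adverse effects, while the definitions speak of events or effects. The article does not say whether the shorter term is meant to be narrower. If it is, unrelated serious events are missing from both statements. If it is not, the section gives two different scopes for serious events.

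The grammar leaves one more doubt: the qualifier could apply to both halves of the opening sentence. That reading would extend the restriction to all adverse effects, so it does not remove the problem.

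**The case against.** The strongest defence is that the sentence is loosely worded and nothing is actually removed. If the qualifier applies only to the serious effects, the first half of the sentence is unqualified and can take in serious effects too; the second half then adds a specific table of treatment-related ones. The closing comparison says any effects, and the section describes no order in which a filter is applied before it. The safety set says who is analysed and the criteria section says what is counted, so the two do not formally contradict each other. And tabulation by causality is detail that an article may leave to the full protocol or analysis plan.

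Much of this stands. The wording is ambiguous, the closing sentence is not expressly filtered, and the tension with the safety set is one of purpose, not strict contradiction. But the point does not rest on missing detail. The article states a restriction, and it is the only statement of which serious effects are analysed as such. Even on the generous reading, a serious event judged unrelated would appear only within a general total of adverse effects and would not be counted as serious.

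A reader might infer something stronger: that a placebo patient, having had no active treatment, can never contribute, so the placebo count is zero by construction. The article does not support that. Under Study design, patients, injecting doctors, assistants and evaluators are blinded, and under Blinding only each centre's pharmacist knows the nature of the box. The article does not say who judges causality or when. If it is judged blind, an event in a placebo patient can be called related. Nor are unrelated serious events lost to the trial: they are still reported to the coordinator.

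**Conclusion.** The point holds as one of wording and scope. The opening sentence of Analysis of safety criteria sets a causality condition on the serious-event count. That condition is inconsistent with the outcome-based definition of a serious event, with the two-arm comparison in the same section, and with the purpose of a safety set that takes in everyone injected. Followed literally, it leaves serious events judged unrelated to BTX-A out of that count in either arm and puts attribution in place of the randomised comparison.

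The conclusion assumes the literal reading of the qualifier. It does not assume that causality is judged unblinded, or that events go uncollected. No numerical size is attached: the effect depends on how many serious events occur and how many are judged unrelated, and the article gives neither. Figures for the precision available at the planned sample size would be the same however the sentence was worded, so they do not measure this defect.

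**What to change.** Reword the opening sentence of Analysis of safety criteria along these lines: *The number and percentage of patients with any adverse event, and with any serious adverse event, will be tabulated and compared by treatment received in both arms, whatever the assessed causality. Events judged related to the study injection will be shown as a subset in both arms.*

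The same term, events, should be used in the closing sentence so that both statements have one scope. The planned non-parametric comparison can stay.

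The cost is a sentence or two of text and a further breakdown in the safety table. No new data are needed, because all adverse events must already be reported. Since the article describes recruitment as under way, the change should be recorded as an amendment, as its section on changes to the planned analysis provides.
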